### 2.8. Statistical Analysis

Descriptive statistics and computations will be performed with SPSS (version 25.0; IBM SPSS Inc., Armonk, IL, USA). Personal data will be kept anonymous.

The normality and homogeneity of data will be checked by applying Kolmogorov– Smirnov and Levene’s tests, respectively. Data will be presented as means and standard deviation (SD) (parametric variables) or median and interquartile range (IR) (nonparametric variables). The independent samples t-test (parametric variables) or the Mann–Whitney U test (non-parametric variables) will be used to determine whether the experimental and control groups were comparable at baseline in terms of participant characteristics. Then, repeated measures of ANCOVA will be applied to analyse the intervention effects on the different dependent variables, adjusted by age and baseline outcomes. Cohen’s d (with a 95% confidence interval) will also be included in the results as the effect size. Effect size thresholds will be interpreted as follows: >0.2, small; >0.5, moderate; >0.8, large [36]. Statistical significance will be computed for the effect of time and the interaction group × time. The alpha level will be fixed at *p* ≤ 0.05.

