### 2.3. Sample Size

Sample size calculations were performed using the G*Power 3.1.9.4 software (Kiel University, Kiel, Germany), selecting the statistical test to compare the difference between two independent means (two groups). Thus, accepting an alpha risk of 0.05 and a beta risk of 0.2 in a bilateral contrast and assuming a moderate effect size of 0.5, a total of 160 participants (80 subjects in the experimental group and 80 in the control group) were sufficient to reach a minimum potency of 90%.

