### 2.7. Measures

A variety of tools will be used. All measures will be undertaken at baseline, at the end of the intervention, and one year after the end of the intervention (follow-up). Before the first measurement, all participants will go through a familiarisation phase to familiarise themselves with the different instruments and assessments included in this project.

a. Anthropometrics and body composition. Bodyweight and height will be assessed. Before the measurements, participants will be asked to remove their shoes, socks, and heavy clothing (coats, sweaters, coats, etc.). They will also be asked to empty their pockets and remove belts and other accessories (bands, pendants, etc.). Height will be measured using a stadiometer (Seca 22, Hamburg, Germany). This instrument must be placed on a vertical surface with the measuring scale perpendicular to the ground. Participants will be positioned in a standing position, with their shoulders balanced, and their arms relaxed along their body. Height will be taken in cm and rounded to the nearest mm. Body weight will be measured using a scale. Body weight will be recorded in kg. and the body mass index (BMI) will be determined using the formula: weight × height^2^.

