Regarding limitations, one of the limitations that will exist for the application of this study is being after/during the COVID-19 pandemic. We must take extra care, by adding space and material for the hygienists, to give greater security to the programme. Travel to the space where the programme will be carried out may also be a limitation, considering that the population under study involves people who no longer travel by car; it may be too far away for them to travel on foot, so there will be increased costs due to the necessity of using public transport.

In the future, it would be interesting to evaluate all age groups, in addition to this age group, such as those who are still actively employed, to have a better perception of what happens throughout life in terms of sensorimotor behaviour, not just during the ageing process. This could result in people being able to act from an early age, to improve the capacities analysed in this study. In addition, it would be interesting to add other clinical variables more related to health, such as blood pressure and cholesterol, because, as reported in other studies [44], there were improvements in these variables in the physical condition of participants. We can also analyse the effects of the programme on the number of medical appointments. Finally, applying a pre-participation physical assessment of the participants by a sports physician would be beneficial.

The added value of this study will be the acquired knowledge about sensorimotor training for the elderly, which will present a scientific advancement for PA, HRQoL, and sedentary behaviour prevention. Finally, it will be innovative in creating an intervention manual and a digital library with specific exercises for sensorimotor training, which allow for better adaptation and motor coordination.

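### Repeated-measures ANCOVA over both post-baseline visits, if fitted in its classical complete-case form, would drop people who miss 18 months from the 6-month comparison; a mixed model avoids this at little cost

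*Protocol article*

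**What the plan says.** Section 2.8 of the protocol article names the method: "repeated measures of ANCOVA will be applied to analyse the intervention effects on the different dependent variables". It adjusts for age and the baseline outcome, tests time and group × time, and uses SPSS 25. It does not name the SPSS procedure, the visits that enter the model, or the treatment of incomplete cases.

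Section 2.7 sets three visits: "All measures will be undertaken at baseline, at the end of the intervention, and one year after the end of the intervention (follow-up"). Section 2.1 includes a one-year follow-up period but lists assessments only before and after the intervention. The Introduction makes the programme effect aim 1 and the follow-up aim 2.

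Section 2.3 sizes the trial by "selecting the statistical test to compare the difference between two independent means (two groups"), "assuming a moderate effect size of 0.5", and arrives at "a total of 160 participants (80 subjects in the experimental group and 80 in the control group"). It states no allowance for dropout. Among the limitations, the Discussion says: "Travel to the space where the programme will be carried out may also be a limitation".

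**The concern.** When the baseline outcome is a covariate, it is no longer a level of the time factor. A time effect and a group × time interaction then need at least two later measurements, and the only two available are the end of the programme and one year after it. The text therefore points to a single model covering both.

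The classical repeated-measures routine works on a complete vector of outcomes and removes anyone with a gap. Someone measured at 6 months but absent at 18 months would be lost from the 6-month effect as well, although the data needed for that effect exist.

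Two things are at stake:

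- **Power for aim 1.** It falls whenever such loss occurs.
- **The randomised comparison at 6 months.** It would be made in people selected by a later event. That does harm if return at 18 months depends on 6-month response differently in the two arms.

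**Working it through.** **1. The plan's own figure.** Inputs from section 2.3: 80 per arm, d = 0.5, two-sided alpha 0.05. For a two-sample t test the noncentrality is d·√(n/2) = 0.5·√40 = 3.16 on 158 degrees of freedom. Power is 88.2% (88.5% by the normal approximation). The article states that 160 "were sufficient to reach a minimum potency of 90" percent. The figure is close, but the design has no reserve above it: 90% needs 86 per arm and 80% needs 64. A total of 128/(1 − 0.20) = 160 would match 80% power with a 20% dropout allowance, but no such allowance is stated. (The same sentence also gives "accepting an alpha risk of 0.05 and a beta risk of 0.2 in a bilateral contrast", which does not agree with 90%. That is a separate matter.)

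**2. Participants lost from the 6-month comparison.** The documents give no loss rates, so these are assumptions: 10% missing from 6 months on, and a further 20% of those remaining missing at 18 months only.

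- All available 6-month data: 160 × 0.90 = 144.
- Complete at both visits: 144 × 0.80 ≈ 115.

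**3. Power with baseline adjustment.** Assume a baseline-to-6-month correlation of 0.5. The adjusted standardised effect is 0.5/√(1 − 0.5²) = 0.577.

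- 72 per arm: noncentrality 0.577·√36 = 3.46, power 93.1%.
- About 57.6 per arm: noncentrality 0.577·√28.8 = 3.10, power 86.7%.

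Simulation of the 6-month ANCOVA (6,000 runs) gives 93.1% and 86.1%.

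**4. Range over other loss rates.** Exact t test, d = 0.5, without baseline adjustment, which is the basis used in section 2.3:

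| Lost by 6 months / by 18 months (assumed) | Per arm: all 6-month data / complete cases | Power: all 6-month data / complete cases |
|---|---|---|
| 5% / 15% | 76 / 68 | 86.5% / 82.5% |
| 10% / 20% | 72 / 64 | 84.6% / 80.1% |
| 10% / 30% | 72 / 56 | 84.6% / 74.6% |
| 15% / 35% | 68 / 52 | 82.5% / 71.4% |

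Baseline adjustment raises all of these by an amount that depends on the correlation, which the article does not give.

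**5. Bias in the 6-month effect.** True effect 0.50, correlation 0.5. A low responder is taken as someone in the bottom third of the arm's own 6-month distribution. Low responders return at 60% and others at 90%, which averages (1/3)(60%) + (2/3)(90%) = 80%. An arm without this pattern returns at 80% at random. ANCOVA estimates among those who return:

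- pattern in the experimental arm only: 0.60;
- same pattern within both arms: 0.50;
- pattern in controls only: 0.40;
- random loss in both arms: 0.50.

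With a median split in place of the bottom third, the experimental-arm-only case gives 0.62. In a separate set-up (correlation 0.6, about 20–25% lost), return depending on the absolute 6-month level by the same rule in both arms gives 0.47. Under a true effect of zero, the experimental-arm-only case rejects in 9.8% of trials, against 4.8% with all 6-month data. That figure belongs to that one scenario.

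**The case against.** The strongest reply is that neither step of the mechanism is written down. Section 2.8 does not say which visits enter the model. Section 2.1 lists only pre- and post-intervention assessments, and the two aims are listed separately. A baseline-to-6-month analysis for aim 1 with a separate follow-up analysis is therefore possible, and loss at 18 months could not then affect aim 1. Complete-case deletion is the default of the classical routine and not a rule in the text; SPSS also offers a mixed model. Handling of missing visits may sit in a fuller document that is not shown, and its absence from an article is no fault.

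Much of this stands, and it makes the point conditional. It does not remove it: a two-visit analysis with baseline as covariate has a single outcome time, so it leaves no time or group × time term of the kind section 2.8 promises to test. The joint model remains the reading that fits the named method best.

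The evidence on dropout is also thin. The travel remark concerns the place where the programme is held, not the 18-month assessment, and says nothing about loss differing by arm. Section 2.6 offers controls the programme when the study ends, which may encourage them to return. On the adjusted assumptions, 86% power is still above the 80% implied by a beta of 0.2, though below the stated 90%.

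A reader might infer that the plan does exclude these participants and so biases aim 1 towards those who return. The documents do not support that. Exclusion is inferred from the method's usual form, and the size and sign of any bias depend on a loss mechanism that they do not describe.

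**Conclusion.** The point holds in conditional form. If the named analysis is fitted as one classical model over the 6- and 18-month visits, every participant seen at 6 but not 18 months is lost from the aim 1 comparison. The power cost follows whenever such loss occurs. It is about 7 percentage points under the main assumed rates with baseline adjustment, and about 4 to 11 points across the unadjusted range shown. All loss rates and the correlation are assumptions.

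Bias is a possibility only: plus or minus about 0.10 SD in the illustrative one-arm scenarios, and none when loss is random or follows the same within-arm pattern in both arms. This is a cheap improvement to the analysis, not a demonstrated flaw in the result.

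**What to change.** Replace repeated-measures ANCOVA in section 2.8 with a linear mixed model for repeated measures, which SPSS provides. Include every randomised participant with any post-baseline value, in the allocated group. Fit group × visit, age, baseline and baseline × visit with an unstructured covariance, and take the 6- and 18-month group contrasts from that model. At minimum, estimate the 6-month effect from all available 6-month data; a separate 6-month ANCOVA would do this.

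State which visits enter the model, and reconcile the assessment schedules in sections 2.1 and 2.7.

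The cost is a change of wording and slightly more modelling, with no new data. The mixed model assumes data are missing at random; a sensitivity analysis for departures from that at 18 months is optional.

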### 2.5. Participants

Participants must meet the following inclusion criteria: (1) be retired; (2) be aged between 55 and 80; (3) show their agreement to participate in the study by providing a signed consent form; (4) be individuals without dentures (except dental prosthesis); and (4) not have undergone surgery for less than six months. Exclusion criteria will be individuals with (1) musculoskeletal diseases; (2) locomotion issues; (3) psychiatric disorders; (4) neurological disorders; and (5) cardiovascular diseases.

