c. HRQoL. This will be assessed using the 36-Item Short-Form Survey (SF-36) [29] in its Portuguese version [30,31], a 36-question tool, which results in 8 dimensions of health status (physical function, physical role, bodily pain, general health, vitality, social function, emotional role, and mental health) and 2 summary components (physical and mental). Dimensions and components are scored from 0 to 100, where 0 is the worst state, and 100 is the best.

d. PAL. This will be assessed using the International Physical Activity Questionnaire Short Form (IPAQ-SF) [32]. This instrument consists of four questions informing on the frequency (days/week) and duration (minutes/day) of daily walks and activities requiring moderate to vigorous physical exertion, as well as the time (minutes/day) spent on sitting activities on weekdays and weekends. PA will be classified into three categories according to the IPAQ consensus group: sedentary (< 600 Met-minutes/week), active (≥ 600 Met-minutes/week), and very active (≥ 3000 Met-minutes/week). This instrument will be completed by the participants in its Portuguese version [33].

e. Subjective Perception of Effort. This will be assessed through the Borg Rating of Perceived Exertion Scale [34] during the sessions, consisting of 10 items for which participants rate their effort from “not at all” (1) to “maximum” (10).

f. Adherence rate. This will be controlled. For this purpose, following previous studies [35,36] the following parameters will be monitored: proportion of participants completing exercise programmes, proportion of exercise sessions attended, average number of exercise sessions completed per week, class attendance expressed as a proportion of participants reaching certain cutoffs, number of weeks in which exercise was undertaken, and proportion of days on which exercise was undertaken. In addition, recommendations from previous studies will be followed to encourage adherence to the programme, including making instructions to subjects simpler and less demanding, addressing cognitive motivational factors such as self-efficacy and health beliefs, offering social support and reinforcement, and providing reminders [37,38].

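### Unless age and baseline score are centred, the planned test of the effect of time is a test at age 0 and baseline 0; section 2.8 should state the centring

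*Protocol article*

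**What the plan says.** Section 2.8 fixes the model: "repeated measures of ANCOVA will be applied to analyse the intervention effects on the different dependent variables, adjusted by age and baseline outcomes". It then names the two tests to be reported: "Statistical significance will be computed for the effect of time and the interaction group × time". The software is named ("Descriptive statistics and computations will be performed with SPSS (version 25.0"), but no procedure or covariate coding is given. The section does not say whether the baseline value is also a level of the time factor.

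Three facts from elsewhere in the article matter here. Participants must "be aged between 55 and 80" (section 2.5). Section 2.7 sets the visits: "All measures will be undertaken at baseline, at the end of the intervention, and one year after the end of the intervention (follow-up". For the SF-36, section 2.7 states: "Dimensions and components are scored from 0 to 100, where 0 is the worst state, and 100 is the best".

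**The concern.** A reader will take a p-value for time to say whether scores changed, on average, between visits. In this model it says so only if the covariates are centred.

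Age and baseline score are constant within a person, so they cancel from any between-visit difference unless the model contains time × covariate terms. Without those terms, the adjustment would touch neither of the two named tests. With them, the time effect is the intercept of a regression of the between-visit difference on group, age and baseline score. An intercept is the expected value where every covariate is zero. If age is entered in years and baseline in its own units, that point is age 0 and score 0. Age 0 is far outside the eligible range, and on the SF-36 a score of 0 is the floor of the scale.

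The pooled time p-values could therefore miss real change or, under some conditions, signal change that did not happen.

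**Working it through.** **The plan's own figure.** The article gives none for the time test. Its only calculation (section 2.3) is for a comparison of two group means, "accepting an alpha risk of 0.05 and a beta risk of 0.2 in a bilateral contrast" and "assuming a moderate effect size of 0.5", with 80 per group. The exact t-test power for those inputs is 88.2%, against a stated minimum of 90%. Only N = 160 is carried forward.

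**Inputs.**
- From the article: N = 160, two equal groups, two-sided 0.05, ages 55-80.
- Assumed: age uniform on 55-80 (mean 67.5, SD 25/√12 = 7.22); outcome SD 1; baseline mean 3 SDs above zero (for example 60 with SD 20); equal correlation r between all visits, r = 0.5, 0.7, 0.85; covariates entered as recorded.

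**Step 1: loss of precision.** With centred covariates the standard error of the intercept is s/√N, where s is the residual SD of the difference. With covariates as recorded it is multiplied by k = √(1 + (mean age/SD age)² + (mean baseline/SD baseline)²) = √(1 + 9.35² + 3²) = 9.87. Age alone gives √(1 + 9.35²) = 9.41, so the loss is nearly as large for outcomes whose baseline mean is near zero.

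**Step 2: 6 versus 18 months, true change 0.3 SD.** Here s = √(2(1 − r)). At r = 0.7, s = 0.775 and the centred standard error is 0.775/√160 = 0.0612, so the test ratio is 0.3/0.0612 = 4.90. Uncentred, it is 4.90/9.87 = 0.50.

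| r | Power, centred | Power, as recorded |
|---|---|---|
| 0.5 | 96% | 6.7% |
| 0.7 | 99.8% | 7.8% |
| 0.85 | 100% | 10.7% |

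With a baseline mean of zero, the uncentred figures are 6.9%, 8.1% and 11.3%.

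**Step 3: 6 versus 18 months, no mean change, change varying with age by 0.1 SD per decade.** The intercept lies 0.01 × 67.5 = 0.675 SD from the true mean change of zero. At r = 0.7 the uncentred standard error is 0.0612 × 9.87 = 0.605, so the ratio is 0.675/0.605 = 1.12. Rejection is 14%, 20% and 35% for r = 0.5, 0.7 and 0.85; centred, about 5%.

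**Step 4: baseline as a level of time, no mean change.** The slope of (6 months − baseline) on baseline is r − 1, so the intercept at baseline 0 is 3(1 − r) SD, which is regression to the mean extrapolated to zero. At r = 0.7 this is 0.9; the residual SD is √(1 − 0.7²) = 0.714 and the uncentred standard error is 0.714 × 9.87/√160 = 0.557, so the ratio is 1.61. Rejection is 60%, 36% and 19% for r = 0.5, 0.7 and 0.85.

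Centring does not fully repair this layout. The mean difference has variance 2(1 − r)/N, but the model uses (1 − r²)/N, which is too small by the factor 2/(1 + r). The centred test therefore rejects 8.9%, 7.1% and 5.9% of the time.

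**Step 5: simulation check (2,000 runs per scenario, r = 0.5, 0.7, 0.85).**

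| Scenario | As recorded | Centred |
|---|---|---|
| 6 vs 18 months, 0.3 SD change | 6.8%, 7.8%, 10.5% | 96.4%, 99.8%, 100% |
| 6 vs 18 months, no change, no age slope | 5.2%, 4.1%, 4.2% | 4.9%, 4.6%, 5.2% |
| 6 vs 18 months, no mean change, age slope | 13.4%, 17.8%, 34.9% | 5.4%, 5.3%, 4.7% |
| Baseline vs 6 months, no change | 57.6%, 35.1%, 19.8% | 8.4%, 6.4%, 5.2% |

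Group × time rejection was identical under both codings in every scenario. Shifting the origin of a covariate changes the intercept and leaves the group coefficient as it was.

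**The case against.** The strongest reply is that the article never says the covariates enter as recorded. Coding is often left to an analysis plan or to program syntax, and a careful analyst would centre. This stands in part: uncentred entry is an assumption, and naming the software does not settle it. It does not dispose of the point, because the article itself fixes the model, the covariates and the time test, and under one of the two ordinary codings that combination does not test mean change.

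A second reply is that time × covariate terms are not mentioned. But without them, covariates that are constant within a person adjust neither named test, so the stated adjustment would do nothing for either.

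A third is that the time effect, pooled over both arms, is not the treatment effect. This stands. A reader might infer that the estimate of programme effectiveness is at risk, or that the second aim (effectiveness through follow-up, section 1) depends on the time test. The article does not support either inference: effectiveness in a parallel-group randomised trial is mainly a between-group question, and group × time does not change with centring.

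A reader might also infer that false positives are certain. They are not. With 6 and 18 months as levels and no age slope, the error rate stays near 5% and only power is lost. Where the baseline mean is near zero, as it could be for the reach tests, the regression-to-the-mean route in step 4 also drops out, although the power loss due to age remains.

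**Conclusion.** The concern holds in conditional form. If age and baseline outcome enter as recorded, the time test named in section 2.8 is evaluated outside the data and does not answer whether mean scores changed. The main consequence is lost power, roughly a fall from near certainty to about one chance in ten or less for a 0.3 SD change. Inflated false rejection is a further risk that depends on whether baseline is a level of time or change varies with age.

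The sizes rest on assumed visit correlations, age distribution, baseline mean and age slope, none of which the article gives. If the analyst centres the covariates, the problem goes away for the 6 versus 18 month comparison; a small excess (up to about 9%) remains if baseline is both a level of time and a covariate. The point is worth correcting because a pre-specified test is affected and the repair is nearly free, but it does not threaten the randomised comparison.

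**What to change.** Add to section 2.8 that age and the baseline outcome are centred at their whole-sample means before entering the repeated-measures ANCOVA, and that the baseline value enters as a covariate only and is not also a level of the time factor. An equivalent to the centring is to state that change over time is tested between estimated marginal means at the mean covariate values, in place of the time main-effect p-value.

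The cost is one sentence and two computed variables per model. No further data or participants are needed. Centring leaves the group × time result as it is; if baseline had been meant as a level of time, the stated time levels would have to be adapted accordingly.

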Research on how PA affects health-related quality of life (HRQoL) has shown that PA’s benefits regarding quality of life were limited [22,23]. Several studies have evaluated the sensorimotor system in the elderly and obtained strength, mobility, and balance improvements, but these results were not consistent due to the reduced sample [20,21], being short-term (12 weeks or less), or only assessing some abilities [17]. This study will last 24 weeks, and its effects will be measured through gait, postural control, strength, flexibility, balance, and agility. Hence, this study will aim to (1) assess the effectiveness of an active retirement programme on elderly body composition, physical fitness, HRQol, and PAL and (2) assess the programme’s effectiveness throughout the ageing process (follow-up).

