## 2. Materials and Methods

### 2.1. Design

A parallel-group randomised controlled trial will be conducted, including a 6-month intervention phase and a 1-year follow-up period. For both groups (control and experimental), assessments will be performed at baseline (before starting the intervention), and after the intervention ends. The study will follow the Consolidated Standards of Reporting Trials Statement (CONSORT) [24].

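### If all three visits enter one baseline-adjusted model, the two tests named in section 2.8 (time, group × time) do not compare the arms at the end of the intervention or at one year

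*Protocol article*

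**What the plan says.** The Introduction sets two aims. The first is to "assess the effectiveness of an active retirement programme on elderly body composition, physical fitness, HRQol, and PAL". The second is to assess the programme's "effectiveness throughout the ageing process (follow-up").

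Section 2.7 gives the visits: "All measures will be undertaken at baseline, at the end of the intervention, and one year after the end of the intervention (follow-up"). Section 2.1 describes a trial "including a 6-month intervention phase and a 1-year follow-up period", but its sentence on timing says only that "assessments will be performed at baseline (before starting the intervention), and after the intervention ends", so the one-year assessment is not listed there.

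Section 2.8 then says that "repeated measures of ANCOVA will be applied to analyse the intervention effects on the different dependent variables, adjusted by age and baseline outcomes". The tests follow: "Statistical significance will be computed for the effect of time and the interaction group × time". Cohen's d with a 95% CI is also planned, without saying which groups or visits it contrasts. The section does not say whether baseline is a level of time as well as a covariate, or whether each later visit has its own model. The t-test and Mann–Whitney test in 2.8 are for comparability at baseline, not for outcomes.

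**The concern.** Each aim needs a difference between the arms at its own visit: the end of the intervention for aim 1, one year for aim 2. The sample size in section 2.3 also rests on a direct comparison of two group means. The named tests need not supply either comparison.

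If baseline is a covariate only, the levels of time are the two later visits. A benefit that lasts in full is then the null hypothesis of group × time, and a trial with a durable effect can be reported as showing no group × time effect. The test is most likely to be significant when the benefit disappears.

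If baseline is also a level, group × time does detect a difference between the arms. However, one p-value covers both later visits, so it cannot be assigned to aim 1 or to aim 2.

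**Working it through.** **Inputs from the protocol.** 80 per arm, effect 0.5 SD, two-sided alpha 0.05 (section 2.3); three visits (2.7); adjustment for age and baseline (2.8).

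**Assumed, not in the protocol.** Unit SD, equal correlation r between visits of 0.3, 0.5 or 0.7, and complete data; 20% loss (64 per arm) as a sensitivity case.

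**The plan's own figure.** For two independent means, the noncentrality is 0.5 × √(80/2) = 3.16, and power ≈ Φ(3.16 − 1.96) = Φ(1.20) ≈ 88.5% (88.2% by exact t). This is close to, though slightly under, the stated minimum of 90%. It is the power of a between-group comparison at one visit.

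**What group × time tests under each reading.** Let Y0, Y1, Y2 be the outcome at baseline, end of intervention and one year. Let b1 and b2 be the baseline-adjusted group differences at the two later visits.

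1. *Separate two-visit fits.* Group × time is the group coefficient in a regression of Yk − Y0 on group, Y0 and age. Adding Y0 to both sides changes only the Y0 coefficient, so the group coefficient and the residuals are those of Yk on group, Y0 and age. The test is exactly bk = 0. In simulation the p-values differed by less than 1e-14.
2. *One model, baseline as covariate only.* Group × time tests b2 − b1 = 0.
3. *One model, baseline also a time level.* Group × time tests b1 = b2 = 0 jointly, on 2 df.

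**Simulation.** 6,000 trials per case, all models adjusted for age and baseline. Each result is the proportion of trials with p < 0.05, at r = 0.3 / 0.5 / 0.7.

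| Per arm | Effect at end, then one year (SD) | Test | Significant |
|---|---|---|---|
| 80 | 0.5, 0.5 | group × time, reading 2 | 0.047 / 0.048 / 0.052 |
| 80 | 0.5, 0.375 | group × time, reading 2 | 0.104 / 0.124 / 0.178 |
| 80 | 0.5, 0.25 | group × time, reading 2 | 0.268 / 0.348 / 0.515 |
| 80 | 0.5, 0 | group × time, reading 2 | 0.741 / 0.872 / 0.980 |
| 80 | 0.5, 0.5 | adjusted contrast, end | 0.907 / 0.955 / 0.992 |
| 80 | 0.5, 0.5 | adjusted contrast, one year | 0.902 / 0.953 / 0.992 |
| 80 | 0.5, 0 | 2-df group × time, reading 3 | 0.864 / 0.936 / 0.993 |
| 80 | 0, 0.5 | 2-df group × time, reading 3 | 0.863 / 0.940 / 0.995 |
| 64 | 0.5, 0.5 | group × time, reading 2 | 0.051 / 0.045 / 0.048 |
| 64 | 0.5, 0.5 | adjusted contrast, end | 0.830 / 0.904 / 0.972 |
| 64 | 0.5, 0.5 | adjusted contrast, one year | 0.839 / 0.902 / 0.972 |

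**Hand checks at r = 0.5, 80 per arm.**

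- *Reading 2, effect wholly lost.* The difference Y2 − Y1 has SD √(2 × (1 − 0.5)) = 1. The noncentrality is 0.5 × √40 = 3.16, so power is about 0.88, against 0.872 simulated.
- *Adjusted contrast.* The residual SD is √(1 − 0.5²) = 0.866. The noncentrality is 3.16/0.866 = 3.65, so power ≈ Φ(3.65 − 1.96) = Φ(1.69) ≈ 0.95, against 0.955 and 0.953.
- *Reading 3.* Given baseline, each later visit has variance 1 − 0.25 = 0.75 and their covariance is 0.5 − 0.25 = 0.25. For 0.5 SD at one visit only, the noncentrality is 40 × 0.5² × 0.75/(0.75² − 0.25²) = 40 × 0.25 × 1.5 = 15, whichever visit carries the effect. This explains the matching rejection rates.

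**The case against.** The strongest reply is that the article never commits to one three-visit model. The abstract and section 2.1 describe assessments before and after the programme, and the Introduction separates effectiveness from follow-up. A baseline/end fit for aim 1 and a baseline/one-year fit for aim 2 would suit that text, and group × time would then be the adjusted contrast itself. Which visits enter which model is detail that a condensed article may leave to the full plan.

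Much of this stands. The separate-fits reading is open and harmless. It is not stated, though, and 2.7 puts all three visits on the same footing, so a single model is at least as natural. Nor does the point rest on silence: 2.8 does say which effects will be tested, and under either single-model reading that list does not match the aims.

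Other replies hold in part:

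- *The 2-df test is a valid between-group test with good power.* True, so it would be wrong to say that no between-group test exists. It still does not locate the visit. The equal rejection rates do depend on assuming equal correlations and effect sizes; the inability to assign one joint p-value to a visit does not.
- *Naming time as a tested effect suggests that baseline is a level, so the 5% figure may not apply.* This is plausible, but adjusting for baseline equally allows the covariate-only reading.
- *Cohen's d with its interval could supply the inference.* It could, if it compared the arms at each visit; 2.8 does not say so and names no test of it.

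**Conclusion.** The point holds in its conditional form. If the three visits enter one baseline-adjusted model, neither named test is a between-group test at the end of the intervention or at one year.

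The harm depends on the reading. With baseline as covariate only, a fully kept benefit is flagged at about the alpha level whatever the correlation or sample size, because the interaction is then truly null. The chance of significance rises as the benefit is lost: 10% to 18% with three-quarters kept, 27% to 52% with half kept, 74% to 98% with none kept. With baseline also a level, an effect is detected but cannot be attributed to either aim. With separate two-visit fits there is no harm.

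The power figures other than the 5% rest on the assumed correlations of 0.3 to 0.7, equal across visits. The plan should be changed, since its named tests may not answer its own aims. Confidence is medium because the text does not settle which reading is intended.

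**What to change.** In section 2.8, take the end-of-intervention and one-year values as the repeated outcomes, with baseline and age as covariates. Name the adjusted between-group difference with 95% CI at the end of the intervention as the test for aim 1, and the corresponding difference at one year as the test for aim 2. Report Cohen's d for these same two contrasts. Keep group × time as a description of whether the effect changed between the two visits.

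If separate two-visit fits are what is meant, say so; in participants with complete data they give the same contrasts. In section 2.1, list the one-year assessment to agree with 2.7.

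The cost is two sentences in 2.8 and one clause in 2.1, with no extra visits or data. The downside is that two contrasts per outcome are reported in place of one interaction.
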